### Data collection and management

Investigators and coordinators will receive specialized training for data collection. All trial-related data will be recorded on study-specific CRFs. In particular, plenty factors, including different stages of cirrhosis, would play an important role in survival of patients with HCC after surgery. Comprehensive clinical data, including Ishak score of the resected specimen, fibrosis-4 index, aminotransferase-to-platelet ratio index, and other parameters for liver cirrhosis to evaluate the baseline stage of cirrhosis, will be prospectively collected. Besides, the death from decompensation of cirrhosis, HCC recurrence, and other reasons will be precisely recorded and recognized during the follow-up since decompensation in patients with cirrhosis is a competing event from HCC recurrence. Baseline assessments will be conducted pre-randomization, and missing data will be stored until received or confirmed as unavailable. Personal information will remain confidential. Data will be entered into Excel by two independent collectors, using participant numbers for identification. Access to information will be restricted. A data manager will oversee routine accuracy checks and address any issues with the investigators. Hard copy documents will be stored securely, and electronic files will have password protection. All documents will be saved for at least 5 years post-publication, with original data available upon request to the principal investigator.

### Statistical analysis

Background measures will be presented as mean ± standard deviation for continuous variables or as numbers/percentages for categorical variables. Continuous variables will be compared using a two-sided student *t*-test or Mann-Whitney *U* test, while categorical variables will undergo the chi-square test or Fisher’s exact test. Patient survival (RFS and OS) will be calculated via the Kaplan-Meier method with log-rank test. In particular, cancer-specific survival will also be calculated since decompensation serves as a competing event from HCC recurrence for death. Stage of cirrhosis, tumor burden, antiviral regimen, and other factors which may affect survival after surgery would be considered when conducting survival analysis. Generalized linear models will analyze primary and secondary endpoints. An ITT analysis, including protocol deviations, will be conducted using IBM SPSS version 26.0 software. A *p*-value < 0.05 indicates statistical significance.

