## Introduction

Hepatocellular carcinoma (HCC) stands as a prevalent malignancy globally [1]. In China, the elevated crude mortality rate of HCC ranks it as the second leading cause of cancer-related death nationally, primarily attributed to endemic chronic hepatitis B virus infection (CHB) [2]. Between 2010 and 2014, the 5-year relative survival rate for Chinese HCC patients was a mere 14.1% [3]. Despite liver resection being the primary treatment for HCC, particularly for those in the early stages with well-preserved liver function, the clinical outcome remains unsatisfactory due to a high recurrence rate. Even in the early stages of HCC, the postoperative 5-year recurrence rate can range from 50 to 70% [4, 5]. Prognostic factors such as tumor size, microvascular invasion, liver cirrhosis, alpha-fetoprotein (AFP) levels, and the viral replication status of HBV influence HCC prognosis [6], with viral load being the most clinically manageable.

Numerous studies have reported that antiviral therapy is associated with a lower HCC recurrence rate after surgical resection [7–9]. For instance, a national cohort study of 4569 patients comparing those with antiviral therapy and untreated patients with resected HBV-related HCC found antiviral therapy to be an independent predictor for lower HCC recurrence [10]. Even in a randomized controlled trial involving patients with low HBV DNA levels, antiviral therapy significantly correlated with improved overall survival (OS) and recurrence-free survival (RFS) [11].

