### Sample size calculation

The sample size calculation was performed using the software PASS (version 2015). The parameters were obtained from our previous randomized clinical trial, which evaluated the efficacy of TDF and ETV in early-stage HBV-related HCC patients after surgery. In that study, the 3-year RFS rates were 70.4% and 82.4% for patients receiving ETV and TDF, respectively. Assuming 3-year RFS rates of 70% for the control group and 85% for the treatment group, with a one-sided alpha of 0.05 and 80% power, the corresponding sample size is 190. Accounting for a 20% dropout rate, a total of 238 patients will be included in this study.

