### Randomization and allocation

Block randomization with a block length of four will be employed. For each block, enrolled participants will undergo 1:1 randomization into the continuing-ETV therapy group and the switch-TDF therapy group. Randomization numbers will be generated using STATA/SE 15.1 and sealed in envelopes.

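### The article names several analyses for RFS, designates none as primary and leaves the covariates open; a short closed list of baseline factors would add some power and settle which result counts

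*Protocol article*

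**What the plan says.** All references are to the Protocol article.

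- **Statistical analysis, test.** "Patient survival (RFS and OS) will be calculated via the Kaplan-Meier method with log-rank test". No strata or covariates are attached, and the test is not called primary.
- **Statistical analysis, covariates.** "Stage of cirrhosis, tumor burden, antiviral regimen, and other factors which may affect survival after surgery would be considered when conducting survival analysis". The list is open-ended, and one item in it, the antiviral regimen, reads as the randomised arm. Under Inclusion criteria every patient enters on ETV monotherapy.
- **Statistical analysis, second method.** Generalized linear models are also named for the primary and secondary endpoints, without outcome form, link or covariates.
- **Randomization and allocation.** "Block randomization with a block length of four will be employed", at 1:1. No stratification factor is named.
- **Introduction.** "Prognostic factors such as tumor size, microvascular invasion, liver cirrhosis, alpha-fetoprotein (AFP) levels, and the viral replication status of HBV influence HCC prognosis".
- **Data collection and management.** FIB-4, APRI, the Ishak score of the resected specimen and "other parameters for liver cirrhosis to evaluate the baseline stage of cirrhosis, will be prospectively collected". Baseline assessments take place before randomisation.
- **Sample size calculation.** "Assuming 3-year RFS rates of 70% for the control group and 85% for the treatment group". The total before dropout is 190, for 80% power when alpha is 0.05 on one side.

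**The concern.** Up to three routes to the primary result are open: a log-rank test without strata, a survival analysis that takes account of prognostic factors, and a generalized linear model. The article does not rank them or close the covariate list. Two things are at stake.

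- **Efficiency.** The article says that tumour size, cirrhosis and AFP influence prognosis, and it collects cirrhosis measures. Neither the randomisation nor the one fully named test uses this information. With about 43 to 54 RFS events expected, some power is given up.
- **Which result counts.** If the unadjusted and adjusted results fall on opposite sides of the significance threshold, nothing in the article says which is the trial's answer. An adjusted result with freely chosen covariates would be hard to defend. The same gap affects the mid-term analysis, which might stop the trial on RFS.

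**Working it through.** **1. The plan's own figure.** Inputs from Sample size calculation: 70% vs 85%, one-sided alpha 0.05, power 80%. Pooled proportion (0.70 + 0.85)/2 = 0.775.

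n per arm = [1.645 × √(2 × 0.775 × 0.225) + 0.842 × √(0.70 × 0.30 + 0.85 × 0.15)]² / 0.15²
= (0.971 + 0.489)² / 0.0225 ≈ 94.8, so 95 per arm and 190 in total.

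Dropout: 190/0.80 = 237.5, so 238. Both figures reproduce exactly from an unadjusted comparison of two proportions. The planned 80% therefore does not rely on covariate adjustment.

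**2. Expected events.** The average 3-year event probability is (0.30 + 0.15)/2 = 0.225. That gives 190 × 0.225 ≈ 43 and 238 × 0.225 ≈ 54 events.

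**3. Power forgone (simulation).** The design inputs are the plan's: marginal 36-month RFS of 70% vs 85%, and blocks of four. The following are assumptions, since the document gives no prognostic hazard ratios: exponential times, three independent binary factors each at 40% prevalence, and an equal hazard ratio for each. The analysis is a Cox model without, then with, the three factors. Two runs of 3,000 to 4,000 trials per setting gave the following at N=190. Ranges span the two runs, and the disagreement column comes from one of them.

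| HR per factor | One-sided 0.05, unadjusted → adjusted | Two-sided 0.05, unadjusted → adjusted | Disagree on two-sided significance |
|---|---|---|---|
| 1.5 | 80% → 81% | 68–69% → 70–71% | 6% |
| 2 | 79–81% → 83% | 69% → 73% | 10% |
| 2.5 | 80–81% → 86% | 69–71% → 77% | 14% |
| 3 | 80–82% → 88% | 70% → 80–81% | 17% |

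Allowing for simulation error, the one-sided gain is about 0 to 4 points for HR 1.5 to 2, and about 5 to 8 points for HR 2.5 to 3.

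**4. Sensitivity: one factor only.** With a log-rank test stratified on one binary factor at 50% prevalence (N=190, one-sided), power moves from 80.1% to 80.9% at HR 2 and from 80.6% to 83.1% at HR 4. The larger gains in step 3 need several strong factors together.

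**5. Chance imbalance without stratification.** With 119 per arm and 40% prevalence, SE = √(2 × 0.4 × 0.6/119) = 0.0635. P(|difference| > 10 points) = P(|Z| > 0.10/0.0635) ≈ 11.5% per factor. For at least one of three, 1 − (1 − 0.115)³ ≈ 31%. The log-rank test's type I error already allows for this. The figures show only why an adjusted result will often be asked for.

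**6. Which factors can be used.** Table 1 places allocation before surgery, and Inclusion criteria admit ablation patients. Ishak score and microvascular invasion need a resected specimen, so they arise after allocation and are unavailable after ablation. FIB-4 and BCLC stage do not have this problem. AFP is itemised under Follow-up, but the pre-allocation row of Table 1 says only that a laboratory test is done, so baseline AFP has to be confirmed.

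**The case against.** The strongest case against is that nothing here is invalid. An unadjusted log-rank test after 1:1 block randomisation controls its error rate, and the stated power is met without adjustment. Adjustment is then an efficiency gain, and a modest one: 5 points or more needs three factors, each with an HR of at least about 2.5. Entry limited to BCLC 0/A, Child-Pugh A and low HBV-DNA narrows the prognostic spread and makes such values less likely. Closed covariate lists and model forms are also commonly left to an analysis plan, which is not shown. All of this stands, and it limits the point. It does not remove it, because the article is not merely silent: it assigns two methods to the same endpoint without ranking them and publishes an open-ended factor list.

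Three stronger readings are tempting and not supported.

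- **That the article commits to an unadjusted log-rank test as its primary analysis.** It does not label that test primary. The same section brings in prognostic factors and generalized linear models.
- **That covariates will be picked by analysts who can see the outcome.** The trial is open-label, but the article says nothing about analyst blinding or when covariates are chosen.
- **That listing antiviral regimen is an error in itself.** A multivariable model must contain the treatment term. The wording only fails to separate that term from the adjustment factors.

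**Conclusion.** The point holds as one of designation and efficiency, not of validity. The article leaves the primary RFS analysis undesignated among several methods and leaves the covariates open, after unstratified randomisation.

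The power forgone is small if the factors are weak and worth having if they are strong. Its size rests on assumed hazard ratios, prevalence and independence of the factors. The two-sided disagreement rate of about 6% to 17% at N=190 rests on the same assumptions and is the more practical reason to act. A reader might infer that the trial is underpowered or that its test is biased for want of stratification. Neither follows, since 190 and 238 are reproduced by an unadjusted calculation.

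**What to change.** In Statistical analysis:

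1. Designate one primary RFS analysis. Either use a Cox model with treatment plus a short closed list of pre-randomisation factors (for example FIB-4 and BCLC 0 vs A, with AFP if it is recorded at the pre-allocation laboratory test), or use a log-rank test stratified by cirrhosis and BCLC stage.
2. Do not use Ishak score or microvascular invasion in that analysis.
3. Keep the Kaplan-Meier curves and the unadjusted log-rank test as supporting.
4. State that antiviral regimen is the treatment term and not an adjustment covariate, and drop the open-ended remainder of the list from the primary model.
5. Say what role, if any, the generalized linear models have for RFS.

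**Cost.** This is a wording change made before outcome data are compared by arm, with no extra patients or visits. There are three small downsides. The Cox hazard ratio becomes conditional on the covariates, the list must stay short for 43 to 54 events, and a rule is needed for missing baseline values.

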### Endpoints

The primary endpoint is 3-year RFS, defined as the interval from the operation to the date of the first diagnosed HCC recurrence, recorded in months. The secondary endpoint is 3-year OS, defined as the interval from surgery to death or the date of the last follow-up, recorded in months.

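### RFS and OS are assigned both to the log-rank test and to generalized linear models, with no ranking, and in its ordinary forms the second method does not handle censoring

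*Protocol article*

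**What the plan says.** All of this stands in the protocol article.

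- *Endpoints*: 3-year RFS is "defined as the interval from the operation to the date of the first diagnosed HCC recurrence, recorded in months". 3-year OS is "defined as the interval from surgery to death or the date of the last follow-up, recorded in months". Both are times, and OS is right-censored by its own definition.
- *Statistical analysis*, first method: "Patient survival (RFS and OS) will be calculated via the Kaplan-Meier method with log-rank test".
- *Statistical analysis*, second method, for the same endpoints: "Generalized linear models will analyze primary and secondary endpoints". No response, distribution, link or offset is given, and neither method is called primary, adjusted or supportive.
- *Statistical analysis*, covariates: "Stage of cirrhosis, tumor burden, antiviral regimen, and other factors which may affect survival after surgery would be considered when conducting survival analysis". No regression model for censored data is named.
- *Statistical analysis*, decision rule: a p-"value < 0.05 indicates statistical significance", not tied to one test. The section also commits to intention to treat.
- *Sample size calculation*: "Accounting for a 20% dropout rate, a total of 238 patients will be included in this study".

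**The concern.** Two methods have a claim on the primary endpoint, and the text gives no order between them. If they disagree, the plan does not say which result is the trial's result. With an open covariate list and one p-value threshold, the choice could be made after the data are seen.

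The second method is also a poor match to the endpoints unless a device for censoring is added. A model fitted to the recorded months treats a patient censored at 10 months like a patient who recurred at 10 months. A model for 3-year status needs a value for every dropout. Excluding dropouts departs from intention to treat, and counting them as recurrence-free understates risk. At stake are the estimate, its power on some readings, and the false-positive rate if dropout differs between arms.

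**Working it through.** **1. The plan's own figure.** Inputs from *Sample size calculation*: 70% versus 85%, one-sided alpha 0.05, power 80%, dropout 20%. The uncorrected two-proportion formula, with mean proportion 0.775, gives per arm

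n = [1.645·√(2·0.775·0.225) + 0.842·√(0.70·0.30 + 0.85·0.15)]² / 0.15² = (0.971 + 0.489)² / 0.0225 ≈ 94.8, so 95.

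The total is 190, and 190 / 0.80 = 237.5, so 238. Both figures reproduce. The trial is thus sized on two 3-year proportions, which makes a binary model a natural reading of the generalized linear model.

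**2. Bias in the ordinary forms, in closed form.** Assumptions not in the document: exponential recurrence and dropout times, independent of each other. Over 36 months the cumulative hazards are −ln 0.70 = 0.3567 (ETV), −ln 0.85 = 0.1625 (TDF) and −ln 0.80 = 0.2231 (dropout).

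Probability of an observed recurrence:
- ETV: 0.3567/0.5798 × (1 − 0.70·0.80) = 27.1%
- TDF: 0.1625/0.3857 × (1 − 0.85·0.80) = 13.5%

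*Binary, dropouts counted as recurrence-free*: difference 13.6 points against a true 15.

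*Binary, dropouts excluded*: 0.2707/(0.2707 + 0.56) = 32.6% and 0.1349/(0.1349 + 0.68) = 16.5%; difference 16.0 points.

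If dropout is instead uniform over 0 to 36 months, the simulated differences are 13.7 and 16.2.

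*Mean recorded months*, 36·(1 − e^−h)/h with h the total hazard:
- True effect, equal dropout: 27.3 (ETV) versus 29.9 (TDF), a difference of about 2.5 months.
- No effect (70% in both arms), dropout 10% versus 30%: h = 0.4620 and 0.7133, giving 28.8 and 25.7. That is a spurious difference of about 3.1 months, larger than the one a true effect produces.

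**3. Simulated error rates.** 119 per arm (238/2), 10,000 trials per scenario, two-sided 5% tests, exponential dropout:

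| Analysis | 70% vs 85%, dropout 20%/20% | 70%/70%, dropout 20%/20% | 70%/70%, dropout 10%/30% |
|---|---|---|---|
| Log-rank | 76.0% | 5.1% | 5.0% |
| Binary, dropouts recurrence-free | 75.7% | 5.1% | 8.7% |
| Binary, dropouts excluded | 75.2% | 5.2% | 7.4% |
| Normal model on months | 40.5% | 5.2% | 51.2% |

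With uniform dropout the first column becomes 76.1%, 75.8%, 75.3% and 42.2%. With a null rate of 77.5% in both arms, uniform dropout and the 10%/30% split, the last column becomes 5.0%, 7.1%, 7.0% and 55.8%. Other assumptions took the months figure as low as 44%, so it should be read as roughly one half.

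In the first scenario the significance verdict differs from log-rank in 3.9% (binary, dropouts recurrence-free), 4.2% (binary, dropouts excluded) and 40.2% (months) of trials.

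**4. Taking either test as positive, no effect, 20% dropout in both arms.** Log-rank or binary: about 6%. Log-rank or months: 8.2% to 8.7%.

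**5. A form that does handle censoring.** A Poisson model with a log person-time offset has about 76% power. It has a 5.0% false-positive rate under the 10%/30% split, and its verdict differs from log-rank in no more than about 1% of trials.

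**6. Timing.** Recruitment ends in May 2024 (*Participant recruitment*) and the study in August 2027 (*Study design*), so every patient can reach 36 months by the final analysis. The mid-term analysis falls one year after the last enrolment, about May 2025 on schedule, when follow-up runs from about 12 to 36 months. Many patients will not have reached 36 months, so neither the binary nor the months model is suitable there.

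**The case against.** The strongest reply is that the sentence does not fix a bad model. Generalized linear models include forms that handle censoring, such as Poisson with a person-time offset or a discrete-time complementary log-log model by visit interval. A reader might infer that one of the two named analyses is invalid. The text does not support that, because the form is not stated. This part of the reply stands.

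A reader might also infer that power is lost whichever form is used. It is not: the binary model, which matches the sample size basis, has nearly the power of log-rank. The large figures belong to a model on raw months, which the document never names. The 10%/30% dropout split is assumed; the protocol gives a single 20%.

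Nor can it be said that about 77% of patients are censored for both endpoints. The figure (70% + 85%)/2 = 77.5% is for RFS only, and no OS rate is given. For 3-year status those patients are known to be event-free, not missing.

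Finally, the covariate list and model details are things a condensed article may leave to an analysis plan that is not shown, and the sentence may be loose wording for the adjusted analysis. That is fair, and their absence is not the finding. The finding is that the published text commits both endpoints to a second analysis, unranked against the first and with no means of handling censoring attached.

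**Conclusion.** The point holds in limited form. The plan assigns censored endpoints to two methods without saying which decides, and the ordinary forms of the second do not handle censoring.

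The consequence ranges widely with the form chosen. For a binary model it is small under equal dropout: an estimate off by roughly 1 point either way, disagreement with log-rank in about 4% of trials, and about 6% false positives if either test counts. It becomes moderate if dropout differs between arms. For a model on months it is severe: power of 40% to 42%, and about half of null trials positive under the assumed unequal dropout. For a Poisson model with an offset it is negligible.

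These figures rest on exponential recurrence times, dropout independent of outcome, and two-sided testing, whereas the design alpha is one-sided. The defect is worth correcting before any comparison by arm, but it does not show that the trial's main analysis is unsound: log-rank is named, and it is adequate.

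**What to change.** In *Statistical analysis*:

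1. State that the log-rank test on RFS, by intention to treat, is the single primary test.
2. Replace the generalized linear model sentence with Cox regression for the hazard ratio, labelled supportive. Use a short list of baseline factors fixed in advance: cirrhosis stage, tumour burden, and AFP if it is measured at baseline. *Follow-up* names AFP only at the post-surgery visits, and Table 1 shows just a general laboratory test before allocation, so this should be confirmed.
3. Report Kaplan-Meier 3-year RFS per arm, with the difference and its confidence interval.
4. Do the same for OS.
5. If a generalized linear model is kept, state a form that handles censoring, such as Poisson with a person-time offset, and label it supportive.

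The cost is wording only. Sample size and data collection do not change, and Cox regression is available in the planned software.

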## Ethics and dissemination

### Ethics approval

The study protocol was approved by the Ethics Committee of West China Hospital, Sichuan University.

### Informed consent

Trained researchers will provide detailed study information, including design, aspects, benefits, and potential harms, to potential participants before enrollment. Enrolled patients will sign written informed consent, ensuring confidentiality of personal information.

### Dissemination

Study findings will be disseminated through national and international conferences as well as peer-reviewed publications.

### Patient and public involvement

No patient is involved.

## Discussion

In the case of most hepatocellular carcinoma (HCC) patients, surgical resection or liver transplantation remains the sole curative modalities. However, the recurrence rate of HCC can ascend to 41–50% within the initial 24 months post-surgical resection (early recurrence) and up to 20% beyond the 2-year mark (late recurrence) [23]. Studies indicate that an elevated viral load is correlated with a heightened HCC recurrence rate and diminished survival post-surgery [4, 24]. Plausible mechanisms suggest that the heightened viral load and hepatic inflammatory activity may contribute to necrosis, ensuing regeneration of residual hepatocytes, inducing DNA mutations, instability, and ultimately fostering HCC recurrence [16]. A mounting body of evidence supporting a favorable prognosis for resected HBV-related HCC with antiviral therapy has prompted international and local clinical practice guidelines to advocate for antiviral intervention pre- and/or post-surgical resection in patients with HBV-related HCC to forestall disease progression and mitigate HCC recurrence [12, 23].

The foremost antiviral agents, namely ETV and TDF, serve as first-line therapies. ETV, a cyclopentyl guanosine analogue, has the potential to inhibit HBV polymerase, achieving a mean 6.9 log decline of serum HBV DNA. Previous investigations reveal a cumulative probability of undetectable HBV DNA at 94–97% with 5-year ETV treatment [25, 26] and 83–90% with 3-year ETV treatment [27–29] in HBeAg-positive patients. TDF, an acyclic adenine nucleotide analogue effective against both HBV and HIV, demonstrates a 3-year cumulative virologic suppression rate of 93.3% in an Asian cohort [30]. Another study reports a 7-year TDF treatment achieving undetectable HBV DNA in 99.3% of HBV patients [31].

As established earlier, antiviral therapy is linked to a reduced HCC recurrence rate post-surgical resection. Current evidence leans towards TDF as a superior choice over ETV in improving HCC prognosis after curative surgery. The potential mechanism behind the lower HCC recurrence rate with TDF therapy, as opposed to ETV therapy, may be attributed to higher serum interferon (IFN)-λ3 levels induced by TDF, but not ETV [32]. IFN-λ has demonstrated antitumor activity in murine HCC models [33, 34], potentially accounting for the divergent recurrence rates observed in patients treated with TDF versus ETV. In a separate in vitro study, TDF pretreatment, unlike ETV, inhibited enteric lipopolysaccharide-mediated production of interleukin (IL)-10 [35], while inducing IL-12. IL-10, an inhibitor of CD8+ T cells, is suppressed, and IL-12 directly stimulates T cells and natural killer (NK) cells. Consequently, TDF therapy may restore the functionality of T cells and NK cells through down-regulating IL-10 and up-regulating IL-12 [16].

Despite prior studies highlighting a superior prognosis with TDF treatment post-surgical resection compared to ETV treatment, these investigations were retrospective and failed to address the necessity of transitioning to TDF therapy after prolonged ETV use. Notably, in China, a nation with a high prevalence of CHB, ETV remains the predominant antiviral drug, constituting nearly 80% of antiviral agents purchased by patients [36]. In clinical practice, many HBV-related HCC patients undergo prolonged ETV therapy before an HCC diagnosis, with TDF potentially overlooked due to economic constraints and concerns about TDF-related renal dysfunction and decreased bone density. Consequently, this study aims to ascertain whether transitioning to TDF treatment post-hepatectomy provides benefits for patients who have received prolonged ETV therapy before surgery. We anticipate that the findings of this study will furnish valuable clinical insights for future treatments.

